# Operational definitions

**Metabolic risk factors of type2 diabetes:** Is the group of biological risks including high central obesity (Body Mass Index or waist circumference), blood glucose, reduced HDL, raised Triglycerides and raised blood pressure (1–3).

**Prevention package:** In this study this term “prevention package” includes health education (risk factors, prevention strategies and impact of the disease) and healthy food plate (recommended portion of carbohydrate, fruits, protein vegetables and cooking oils) (4,5).

**Street-vended foods:** Foods or beverages sold after being prepared on the street or at home and ready to eat or to be consumed immediately or later on the street/public places without further processing or preparation(6,7).

**Street food consumer:** Is a person who buys and eat foods or drink beverages prepared in the street or at home and sold in the streets/public areas (6,7).

**Regular street food client:** A person who consume at least three street vended lunches per week ***(to be operationalized and validated later)***

**Effectiveness of intervention:** refers to performance of an intervention in producing the intended outputs/outcomes

**Unhealthy diet**: Meals consumed in a day with less than two servings of fruits, less than five servings of vegetables, more than half plate of carbohydrate and protein(8).

**Unhealthy eating behaviours:** A practice of eating foods or drinks to feel full and satisfied without considering the amount of food or drink if it is appropriate or not (9)**.**

**Healthy food plate**: A plate that guides every person on healthy eating habits showing the recommended proportion and types of foods or drink that are to make up a healthy and balanced diet (4,5)**.**

**Components of Healthy plate:** Half meal vegetables and fruits, ¼ whole grains, ¼ proteins, cooked with healthy plant oils and drinking water(4,5)**.**

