1.0 Introduction and Background: Type2 diabetes is a global public health problem (10–12). The global prevalence of the disease in 2014 was 8.5% and the number of people living with the disease is expected to increase from 415 million in 2015 to 642 in 2040; a 55% increases if effective intervention programs will not be put in place (12). In Sub Saharan Africa the prevalence is ranging from 1% to 12% while in Tanzania the prevalence of type2 diabetes has increased from less than 1% in 1989 to 9.1% in 2012 (10,11,13,14). According to the global burden of diseases in Tanzania diabetes was among the top 20 killer diseases in 1990 but in 2016 is among the top ten killer diseases (<https://vizhub.healthdata.org/gbd-compare/> **See Appendix A**). Contrary to the middle and high income countries; the prevalence of the diseases by age in the low income countries seems to decrease by increase in age due to premature deaths(12). Type2 is associated with acute complications including kidney failure, amputation, blindness, stroke, impotence plus deaths(11,15).These complications impose cost burden in the health system and at family level (15). In 2012: Diabetes and higher blood glucose caused 3.7 million deaths and 43% of these deaths were premature (11). The risk factors of type2 diabetes are divided in three categories including metabolic/ intermediate, behavioural and socio-economic and familial (16,17). Metabolic risk factors includes raised blood pressure (BP), raised triglyceride (TG), high blood glucose (BG) low high density lipoprotein (HDL) and central obesity(1–3). Physical inactivity, unhealthy diet, smoking and harmful alcohol consumption are the components of behavioural risk factors of the diseases (14,16,17). Socio-economic and familial risk include sex, age, income, location, knowledge and family history of the disease (16–18). The burden of metabolic and behavioural risk in Tanzania is evident; a national STEPs survey of 2012 in Tanzania indicated among that among individuals aged 25-64; 34.7% were overweight/ obese, 26% had raised total cholesterol, 26% had raised blood pressure and 33.8% had raised triglycerides. The survey also showed that tobacco users were 15.9% and alcohol drinkers were 29.3%. Almost all 5680(97.2%) of the participants consumed less than 5 servings of fruit and/or vegetables on average per day (14). Another study conducted in Mwanza among adults; 44.7% were overweight /obese and 36.3% had raised Blood Pressure (19). In Kilimanjaro among participants aged 18 and above 31% had raised blood pressure, 58% were overweight /obese, current drinkers (41.2%) and 21.7% were found with glucose impairment (20). In a recent study in Ifakara nearly 82% of the participants did not meet the recommended daily fruits and vegetables intake (21). Another study conducted in Dar es Salaam and Mbeya among HIV positive clients also reported high prevalence of low HDL (71.9%), raised triglyceride (16.6%), overweight/obese (26.2%), central obesity (46.6%), alcohol consumption (32.9%), low level of fruits and vegetable consumptions (70%) and low physical activity (47.8%) (18).

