2.6.1 Magnitude of type2 diabetes, behaviourial and its risk factors: The prevalence of type 2 diabetes among urban street cooked food consumers will be determined. A person will be considered to have diabetes if the reading for fasting blood glucose measured using Accu-check machine is >7.0mmol/L or is on medication for raised blood glucose. This study will also assess the prevalence metabolic and behavioural risk factors of type 2 diabetes. Prevalence of metabolic risk factors will be assessed as follow: being overweight or obese (BIM≥25Kg/M^2^), raised TC (≥5.1mmol/L), raised TG (≥2 mmol/L), low HDL (<1.03 mmol/l for Male and < 1.29 for Female), raised LDL (>2.6 mmol/L), Abnormal Waist Hips Ratio for male and female if the value is >0.8 and >0.9 respectively, raised Systolic BP (≥140mmHg) and Diastolic BP (≥90 mmHg) (17,18). Behaviorial assessement will including participating in physical activities as per recommended standard (≥600MET/week), Behaviourial assessment will include consumption of fruits and vegetables as per standard (≥5 days per week), non-harmful drinking (5 or less for male and 4 or less for female units of alcohol per week) and not consuming table salt will be assessed (18,52).

**Blood Pressure (BP) Measurements**: Blood pressure will be measured while patients are in a sitting position, using an M4 Omron® device. An average of the last two readings taken three times consistently after three minutes from the left arm will be treated as final reading and will be used during analysis(18). The final will be classified as raised blood pressure if BP of ≥140/90mmHg.

**Weight Measurement**: SECA® weighing scale will be used to measure weight. Participant will be asked to remove any heavy clothing (such as coats and shoes) and stand still on the weighing scale, with hands by their sides.

**Height Measurement:** Height will be measured with a SECA® stadiometer, while a patient is facing directly ahead. Patients will be instructed to remove their shoes, caps or head scarf, keep their feet together, and stand with their arms by the sides. Measurement will be taken with heels, buttocks and upper back in contact with the stadiometer.

**Body Mass Index (BMI):** The product of weight (in Kilograms) divided by height squared (m^2^) will give BMI. Categorization BMI will be as follows ; obesity is ≥30 kg/m2; Overweight if the BMI is > 25 but < 30kg/m2, and normal if the BMI is between 18-25kg/m2 and underweight if below 19 kg/m^2^ (53).

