**Waist circumference:** The measurement will be done according to WHO guidelines where by measurement will be taken at the approximate midpoint between the lower margin of the last palpable rib and the top of the iliac crest (54). The values will be grouped as follows abnormal waist circumference of male and female are >94 cm and >80 cm respectively ; this classification is according to World Health Organizations (WHO) and International Diabetes Federation (IDF) recommendations(1,3).

**Hips measurements:** Hip measurement is one of an important parameter for monitoring weight gain or loss. Participant will be asked to remove heavy garments and put the feet together then soft measuring tape will wrapped and snag around the widest part of his/her hips. Then the value of hip measurement is the point at which the end of the tape meets the remaining length.

**Waist Hips Ratio**: Waist to hip ratio is a measure of how fat is distributed around the body. It is calculated by dividing waist to hips values. Waist Hips Ratio will be considered normal for male and female if the value is ≤0.8 and ≤0.9 respectively(55).

**Laboratory Tests**: Study participants will be requested to return to the clinics to provide fasting blood samples for blood glucose and lipid profile (TC, HDL and Triglyceride) tests in the following day after fasting for at least 8 hours. The tests will be performed by trained laboratory technicians.

**Fasting Blood Glucose:** Blood sample will be taken by finger prick (capillary) and measured using Accu-check machine. Raised fasting blood glucose will be considered if the result is >7.0mmol/L (19,20)**.**

**Lipid profile testing:** Blood sample will be collected for testing HDL-C, HDL-C, TC, and TG-C. Blood will be kept at room temperature and will be analyzed the same day using fully automated biochemistry analyzers by the direct end point enzymatic method.

**Alcohol drinking**: Participants will be interviewed on the history of alcohol drinking and those who will be found currently drinking will be asked further questions. These questions will include age when started drinking, frequency of drinking and amount taken on average when they drink.

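### Section 2.6.1 fixes cut-offs for waist-hip ratio, fruit and vegetable intake and BMI that conflict with the rest of the protocol and would distort the objective 1 prevalences

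*Protocol*

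**What the plan says.** **Waist-hip ratio.** Section 2.6.1 of the Protocol defines "Abnormal Waist Hips Ratio for male and female if the value is >0.8 and >0.9 respectively". Its Waist Hips Ratio paragraph repeats the rule from the other side: "Waist Hips Ratio will be considered normal for male and female if the value is ≤0.8 and ≤0.9 respectively". For waist alone the same section has "abnormal waist circumference of male and female are >94 cm and >80 cm respectively".

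**Fruit and vegetables.** Section 2.6.1 sets "consumption of fruits and vegetables as per standard (≥5 days per week". Its later paragraph on fruit and vegetables says that intake follows WHO standards and collects both days and servings. The operational definition of an unhealthy diet counts daily servings: "less than two servings of fruits, less than five servings of vegetables". Section 1.0 describes almost all respondents in the national survey (97.2%) as having "consumed less than 5 servings of fruit and/or vegetables on average per day". Section 2.7.1 teaches participants an amount in servings per day. Section 2.6.4 compares the arms on the mean number of days per week on which fruit or vegetables are eaten.

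**BMI.** Section 2.6.1 has "normal if the BMI is between 18-25kg/m2 and underweight if below 19" (kg/m²). Overweight or obese is ≥25 in the prevalence rule, but overweight is >25 in the classification further down. The participant feedback form in Appendix B uses <18.5, 18.5–24.9, 25–29.9 and ≥30.

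**The concern.** Specific objective 1 is the prevalence of metabolic and behavioural risk factors, and the first planned paper reports it. Section 2.6.4 also plans logistic regression. Both need each participant to fall in one class only, and in the class that the protocol means.

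These rules are written out in full, so a later analysis plan would contradict the protocol if it changed them. If they are followed as they stand, two measures of central obesity rank the sexes in opposite ways. A diet far below the protocol's own benchmark counts as adequate. Some participants belong to two BMI classes.

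**Working it through.** **1. Waist-hip ratio against waist**

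The protocol says of the ratio: "It is calculated by dividing waist to hips values", so ratio = waist / hip. Put the waist limits into it:

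- Man at 94 cm: the ratio is normal (≤0.8) only if the hip is at least 94 / 0.8 = 117.5 cm.
- Woman at 80 cm: the ratio is abnormal (>0.9) only if the hip is below 80 / 0.9 = 88.9 cm.
- With the labels exchanged, the same hip limits are 94 / 0.9 = 104.4 cm for men and 80 / 0.8 = 100.0 cm for women, which lie much closer together.

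The rule appears twice with the same labels, so it is not a slip in one place.

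How many participants would change class? Those with a ratio between 0.8 and 0.9. Table 1 gives a mean of 0.82 and an SD of 0.2, not split by sex. Assume a normal distribution common to both sexes:

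Share = Φ((0.9 − 0.82)/SD) − Φ((0.8 − 0.82)/SD)

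| SD | Source | Calculation | Share |
| --- | --- | --- | --- |
| 0.20 | Table 1 | Φ(0.40) − Φ(−0.10) = 0.655 − 0.460 | 19.5% |
| 0.10 | assumed | Φ(0.80) − Φ(−0.20) = 0.788 − 0.421 | 36.7% |
| 0.08 | assumed | Φ(1.00) − Φ(−0.25) = 0.841 − 0.401 | 44.0% |
| 0.05 | assumed | Φ(1.60) − Φ(−0.40) = 0.945 − 0.345 | 60.1% |

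**2. Fruit and vegetables**

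- One serving on each of five days meets the rule: 5 × 1 / 7 = 0.71 servings per day.
- If the rule means fruit and vegetables each on five days, the least that passes is (5 + 5) / 7 = 1.43 servings per day.
- The survey benchmark in section 1.0 is 5 per day.

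Qn76 to Qn79 collect days and servings separately for fruit and vegetables, so mean servings per day can be derived as (Qn76 × Qn77 + Qn78 × Qn79) / 7. One obstacle is in the form: Qn77 and Qn79 ask for servings, but their response lines ask for a number of days, in both the English and the Swahili versions.

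**3. BMI**

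Values from 18 to below 19 meet both the normal and the underweight rule. With Table 1's mean of 22.9 and SD of 4.6, and a normal distribution:

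- Φ((19 − 22.9)/4.6) − Φ((18 − 22.9)/4.6) = 0.198 − 0.143 = 0.055.
- 0.055 × 556 is about 31 participants, and the class shares add up to 105.5%.
- Underweight is 19.8% with the limit at 19 and 16.9% with the feedback form's 18.5.

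A BMI of exactly 25 is overweight under one rule of section 2.6.1 and normal under the other.

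**The case against.** **The waist-hip labels are not proved wrong.** A ratio and a length are different scales, and the two statements of the ratio rule agree with each other. This stands: the opposite ordering is a strong warning, and the cited report has to settle it. A reader might infer that prevalence is overstated in men and understated in women by about 20 points each. The documents do not support that as a finding. It needs the exchange to be confirmed, and it gives both sexes the same distribution, which Table 1 does not state. The SD of 0.08 behind the 44% is not in the protocol.

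**The effectiveness analysis does not use these cut-offs.** Section 2.6.4 compares metabolic means, and Table 4 does not list the waist-hip ratio as a dependent variable. Raw height, weight, waist and hip are recorded, so participants can be reclassified later. This stands, and it limits the point to prevalence and logistic models.

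**Days may respond to the intervention.** A reader might infer that the plate changes the portion more than the number of days, so that the outcome in section 2.6.4 is insensitive. Nothing in the protocol shows this. Section 2.1 says that vendors rarely serve fruit, and section 2.3 puts fruit on the plate, so days could well rise. What remains is narrower: days alone cannot register a larger portion. The diet items also refer to an ordinary week over the previous year, so servings would not by themselves give a sharp three-month measure either.

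**The 18–19 BMI overlap is minor.** Underweight is not one of the listed risk factors. That is fair. The conflict at exactly 25 does touch a listed one, though it will concern few participants.

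**Conclusion.** The point holds for the definitions. Section 2.6.1 contains three sets of cut-offs that disagree with other parts of the protocol, and applying them as written would give distorted or inconsistent prevalences for objective 1.

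- **Waist-hip ratio:** the sex labels appear exchanged, subject to reference 55. About 20% of participants would change class under Table 1's values, and 37% to 60% for assumed SDs of 0.10 to 0.05. All of these are illustrations that rest on a normal distribution shared by both sexes.
- **Fruit and vegetables:** the rule passes an intake of about 0.7 servings per day (1.4 on the stricter reading), against a benchmark of 5.
- **BMI:** about 5.5% of participants fall in two classes under Table 1's values, and the value 25 is classified in two ways.

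The between-arm comparison of metabolic means is not affected. These are corrections that should be made before prevalence is analysed; they do not call the trial design into question.

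**What to change.** 1. Check both waist-hip statements in section 2.6.1 against the report cited as reference 55. If it confirms the exchange, correct the sex labels in both places. If it does not, say why the ordering differs from that of the waist limits.
2. Define fruit and vegetable adequacy as mean servings per day, from days × servings / 7 summed over fruit and vegetables (Qn76 to Qn79). State one threshold, for example the 5 per day of the source survey in section 1.0. Reconcile it with the operational definition of an unhealthy diet, which uses two servings of fruit and five of vegetables.
3. Correct the response lines of Qn77 and Qn79 in both languages so that they record servings.
4. In section 2.6.4, report mean servings per day beside mean days per week.
5. Use one non-overlapping set of BMI classes throughout, such as that on the feedback form, written as <18.5, 18.5 to <25, 25 to <30 and ≥30.

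The cost is small: changes to the protocol text and to two items on the form in each language. No new measurement is needed. The form has to be corrected before data collection, because a count of days entered at Qn77 or Qn79 cannot be turned into servings afterwards.

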| 7.Site preparation |  |  |  |  |  |  |  |  |  |  |  |  |
| 8.Finalize protocol |  |  |  |  |  |  |  |  |  |  |  |  |
| 9.Supervisory and Mentorship |  |  |  |  |  |  |  |  |  |  |  |  |
| 10.Baseline data collection |  |  |  |  |  |  |  |  |  |  |  |  |
| 11.Implement intervention package |  |  |  |  |  |  |  |  |  |  |  |  |
| 12.Data management and analysis for baseline |  |  |  |  |  |  |  |  |  |  |  |  |
| 13.Defend Thesis |  |  |  |  |  |  |  |  |  |  |  |  |
| 14. End line data collection |  |  |  |  |  |  |  |  |  |  |  |  |

2.11 Ethical consideration: An ethical clearance will be sought from the Medical Research Coordination Committee of the National Institute for Medical Research. Regional and district authorities will be informed about the aim and procedures of the study. During the study, participants will be informed about the aims and benefits of the study and a written informed consent will be obtained from each participant. Names will not be used and confidentiality will be maintained by keeping data collection questionnaire locked in a secure cabinet, while the electronic data file will be kept in a password protected computer. Participants who will be examined and identified with hypertension, or diabetes (high blood sugar) will be referred to the nearest health facilities for further management. Those who will be screened and found with abnormal cholesterol and body mass index will be counselled and advised on proper approaches for risk prevention and control. This protocol will be registered in order to comply with WHO’s  [Helsinki](http://www.wma.net/en/30publications/10policies/b3/index.html) Declaration which states that "Every clinical trial must be registered in a publicly accessible database before recruitment of the first subject".

Table 6 Budget for the study project

| **S/No** | **Item** | **Description** | **Year1 (Euros)** | **Year2 (Euros)** | **Year3 (Euros)** | **Total (Euros)** | **Source** |
| --- | --- | --- | --- | --- | --- | --- | --- |
| 1 | Salary/Stipend | 36 months | 4,560 | 4,560 | 4,560 | **13,680** | ASPIRE |
| 2 | Tuition Fees |  | 5,200 | 5,121 | 5,120 | **15,442** | ASPIRE |
| 3 | Training / Workshop | Pm | - | - | - | **-** | Vliruos/others |
| 4 | Supervision | Lump sum | 381 | 381 | - | **762** | ASPIRE |
| 5 | Research cost (lab) | Lump sum | 19,650 | - | - | **19,650** | ASPIRE/others |
| 6 | Equipment(lab) | Lump sum | 762 | - | - | **762** | ASPIRE/others |

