**Section F: Step 2 Physical Measurements**

| **Q-Number** | **Question** | **Response** | **Code** |
| --- | --- | --- | --- |
| **Height and weight** | | | |
| 105. | Device IDs for height and weight | a)Weight:_____ | Qn105a |
|  |  | b) Height:______ | Qn105b |
| 106. | Height (cm) | ______.____ | Qn106 |
| 107. | Weight (kgs) | ______.____ | Qn107 |
| **Waist Circumference** | | | |
| 108. | Device ID for waist | ___________ | Qn108 |
| 109. | Waist circumference (cm) | ______.____ | Qn109 |
| **Blood Pressure** | | | |
| 110. | Device ID for blood pressure |  | Qn110 |
| 111. | Cuff size used: 1. Small 2. Medium 3. Larger |  | Qn111 |
| 112. | Reading 1 a) Systolic ( mmHg) | __________ | Qn112a |
|  | b)Diastolic (mmHg) | __________ | Qn112b |
| 113. | Reading 2 a) Systolic ( mmHg) | __________ | Qn113a |
|  | b)Diastolic (mmHg) | __________ | Qn113b |
| 114. | Reading 3 a) Systolic ( mmHg) | __________ | Qn114a |
|  | b)Diastolic (mmHg) | __________ | Qn114b |
| 115. | During the past two weeks, have you been treated for raised blood pressure with drugs (medication) prescribed by a doctor or other health worker?   1. Yes 2. No |  | Qn115 |
| **Hip Circumference** | | | |
| 116. | Hip circumference (cm) | __________ | Qn116 |

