**Section G: Step 3 Biochemical Measurements**

| **Q-Number** | **Question** | **Response** | **Code** |
| --- | --- | --- | --- |
| **Blood Glucose** | | | |
| 117. | During the past 12 hours have you had anything to eat or drink, other than water? 1. Yes 2. No |  | Qn117 |
| 118. | Technician names (initials) | ___________ | Qn118 |
| 119. | Device ID | ___________ | Qn119 |
| 120. | Time of day blood specimen taken (24 hour clock) | Hours :  minutes | Qn120 |
| 121. | Fasting blood glucose: *(mmol/l)* |  | Qn121 |
| 122. | Today, have you taken insulin or other drugs (medication) that have been prescribed by a doctor or other health worker for raised blood glucose?  1. Yes 2. No |  | Qn122 |

| **Q-Number** | **Question** | **Response** | **Code** |
| --- | --- | --- | --- |
| **Blood Lipids** | | | |
| 123. | Device ID |  | Qn123 |
| 124. | Total cholesterol *(mmol/l)* |  | Qn124 |
| 125. | During the past two weeks, have you been treated for raised cholesterol with drugs (medication) prescribed by a doctor or other 1. Yes 2. No |  | Qn125 |
| 126. | Triglycerides  *(mmol/l)* |  | Qn126 |
| 127. | During the past two weeks, have you been treated for raised Triglycerides with drugs (medication) prescribed by a doctor or other 1. Yes 2. No |  | Qn127 |
| 128. | High Density Lipoprotein *(mmol/l)* |  | Qn128 |
| 129. | During the past two weeks, have you been treated for low High Density Lipoprotein s with drugs (medication) prescribed by a doctor or other 1. Yes 2. No |  | Qn129 |
| 130. | Low Density Lipoprotein *mmol/l)* |  | Qn130 |
| 131. | During the past two weeks, have you been treated for raised Low Density Lipoprotein with drugs (medication) prescribed by a doctor or other  1. Yes 2. No |  | Qn131 |

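### Treated participants can drop out of the diabetes and raised-blood-pressure categories: glucose drugs are asked about only for the day of a fasting visit, and blood pressure is classed by reading alone although treatment is recorded

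*Protocol*

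**What the plan says.** **Definitions (Protocol 2.6.1).** A person has diabetes if the fasting reading "is >7.0mmol/L or is on medication for raised blood glucose". For blood pressure, after the averaging of the last two readings, the rule is: "The final will be classified as raised blood pressure if BP of ≥140/90mmHg". The list of metabolic risk factors earlier in 2.6.1 also defines raised systolic and diastolic pressure by threshold only. Under Fasting Blood Glucose there is a second glucose category, again without treatment: "Raised fasting blood glucose will be considered if the result is >7.0mmol/L". The cholesterol and triglyceride categories are thresholds only.

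**What the form collects (Appendix B).** Qn115 asks about drug treatment for raised blood pressure in the past two weeks. Qn125, Qn127, Qn129 and Qn131 use the same two-week window for the lipids. Glucose differs. Qn122 reads "Today, have you taken insulin or other drugs (medication) that have been prescribed by a doctor" and so on. It sits in Section G, which goes with the blood samples. According to 2.6.1 (Laboratory Tests), these are taken on the following day after at least 8 hours of fasting. Qn102-104 ask whether glucose was ever measured and whether diabetes was diagnosed, not whether it is treated.

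**Referral and use.** Under 2.11, participants identified with hypertension or diabetes "will be referred to the nearest health facilities for further management"; no arm is named. Section 2.3 repeats the baseline measurements at endline. Section 2.10 expects the effect of the package on the prevalence of metabolic risk factors to be known. Section 2.6.4 compares means by t-test, uses mixed models for the pre-post analysis, and adds linear and logistic regression at baseline and endline.

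**The concern.** There are two separate weaknesses.

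First, the diabetes rule needs to know who is on medication, and the item that should supply this has a window too short for the moment at which it is asked. A person who comes fasting may well not have taken that day's drug. If the reading is also 7.0 mmol/L or less, because the treatment works, neither half of the rule catches that person.

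Second, raised blood pressure ignores a treatment item that the form already contains. A participant on drugs and below the threshold is classed with people who never had the condition.

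At stake are the prevalence estimates of Objective 1, any logistic model with one of these categories as outcome, and the before-after reading of prevalence that 2.10 invites. The glucose weakness cannot be repaired at the analysis stage, because the information will not have been collected.

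**Working it through.** The protocol states no figure on this point, so there is none to reproduce. The check sets the rules against the items and then shows a range under stated assumptions.

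**1. Rule against item**

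| Category | Rule in 2.6.1 | Treatment item | Window | Item used in the rule? |
| --- | --- | --- | --- | --- |
| Diabetes | Reading or medication | Qn122 | Same day, fasting visit | Yes, but too narrow |
| Raised fasting glucose | Reading only | Qn122 | Same day, fasting visit | No |
| Raised blood pressure | Reading only | Qn115 | Two weeks | No |
| Lipid categories | Reading only | Qn125-131 | Two weeks | No |

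The Swahili form has the same windows: that day for glucose, two weeks for blood pressure and lipids.

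**2. Direction.** Let R be the set with a reading at or above the threshold, and T the set on treatment. The share in R can never exceed the share in R or T, and the gap is the share treated and below the threshold. So the reading-only prevalence is equal to or below the treatment-inclusive one. For diabetes, the gap is the share treated, with no drug taken that day, and reading 7.0 mmol/L or less.

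**3. Size for Objective 1 (illustration).** Input from the protocol: 26% with raised blood pressure in the national survey cited in section 1.0. Assumptions: 26% is taken as the reading-only prevalence, and a further share c of all participants is treated and below the threshold. The documents give no value for c.

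Inclusive prevalence = 26% + c; relative understatement = c / (26% + c).

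| c (assumed) | Inclusive prevalence | Relative understatement |
| --- | --- | --- |
| 1% | 27% | 0.01/0.27 = 3.7% |
| 3% | 29% | 0.03/0.29 = 10.3% |
| 5% | 31% | 0.05/0.31 = 16.1% |

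**4. Before-after fall from referral (illustration).** Assumption: a fraction f of those raised at baseline is on drugs and below the threshold at endline, and the package has no effect. Endline reading-only prevalence = 26% × (1 − f). People moved per arm = 278 × 0.26 × f.

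| f (assumed) | Endline prevalence | Fall in points | People per arm of 278 |
| --- | --- | --- | --- |
| 10% | 23.4% | 2.6 | 7.2 |
| 30% | 18.2% | 7.8 | 21.7 |
| 50% | 13.0% | 13.0 | 36.1 |

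A rule that counts treated people stays at 26% throughout. If f is the same in both arms, the fall is the same in both, and the difference between arms at endline remains zero.

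**The case against.** **The scheme may be deliberate.** Diabetes is a disease, defined by reading or treatment; the risk factors are current levels, defined by reading. The reading-only rule for raised fasting glucose fits that view. This stands in part: the blood pressure rule is an arguable choice and not a contradiction, which is why the reading-only figure should be kept. It does not answer the diabetes point, where the protocol's own criterion and its own item do not match.

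**Medication handling can wait for the analysis plan.** This is true for blood pressure and lipids so far as the data go, although the protocol already fixes the category. It is not true for glucose. The biochemical feedback form has a box for current medication, but it is a feedback sheet to the participant, not an analysis item, and it states no window.

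**The numbers are assumed.** This stands in full. The 26% is a national figure, and the protocol does not show whether it already includes treated people. Nor does everyone at 140/90 or above necessarily get referred: 2.11 gives no threshold, and the feedback form separates 140-159/90-99 from 160/100 and above.

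**A stronger reading to resist.** A reader might infer that referred participants count as improved and that the trial would therefore credit the package with an effect it did not have. The documents do not support that. Referral applies without regard to arm, and no reason is given for different drug uptake. Only someone treated and below the threshold changes category, and a person who reports glucose medication that day still counts as diabetic. The stated effectiveness comparison is of means. Drug effects may enter those means, but redefining a category neither causes nor cures that.

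**Conclusion.** The point holds for classification and prevalence, not for the comparison between arms. Qn122 cannot deliver the medication half of the diabetes rule, and the blood pressure rule discards treatment information that is collected. Prevalence of both can only be equal to or below a treatment-inclusive figure. Any categorical model of blood pressure inherits the misclassification, although 2.6.4 does not say which outcomes will be dichotomised.

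A reading-only category can also fall between baseline and endline in both arms because of drug starts after referral.

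The size is unknown. The ranges shown (27-31% instead of 26%; falls of 2.6 to 13.0 points) rest wholly on assumed treatment shares and on using the cited 26% as a reading-only baseline. The size of the group missed by Qn122 cannot be estimated at all from the documents.

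**What to change.** - **Qn122:** ask about glucose-lowering drugs in the past two weeks, as Qn115 and Qn125-131 do, in the English and Swahili forms. This has to be done before baseline data collection.
- **Raised blood pressure:** for Objective 1 prevalence and for categorical analyses, report it as average systolic ≥140 mmHg or average diastolic ≥90 mmHg or Qn115 = yes. Keep the reading-only figure as secondary.
- **Lipid categories and raised fasting glucose:** treat them in the same way, using Qn125-131 and the revised Qn122.
- **Interpretation:** state that a before-after fall in reading-only prevalence will not be read as an effect of the package.

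The thresholds are the protocol's own, and nothing here touches referral or treatment. The cost is one question stem in two languages and a few sentences in 2.6.1 and 2.6.4. The blood pressure and lipid treatment items are already on the form.
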